**Methods:**

We plan to enrol 164 newly diagnosed MDR-TB patients aged ≥ 8 years from three regional hospitals based in rural and urban Uganda. Patients with conditions that affect their dexterity and ability to operate the MEMS-operated medicine equipment will not be eligible to participate in the trial. Patients are randomized to either of the two study arms: self-administered therapy with adherence being monitored using MEMS technology (intervention arm) or health facility-based DOT (control arm) and will be followed up monthly. Adherence is measured by the number of days the medicine bottle is open to access medication as recorded by the MEMS software in the intervention arm and treatment complaint days as recorded in the TB treatment card in the control arm. The primary outcome is the comparison of adherence rates between the two study arms.

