#### Diagnosis and management of MDR-TB

Diagnosis of MDR-TB is based on Gene Xpert® testing of sputum for identification of resistance to rifampicin (RR-TB) followed by culture and drug susceptibility testing (DST) for phenotypic characterization; however, treatment is started prior to the receipt of culture and sensitivity results due to long turnaround time of 10–16 weeks. Treatment options for MDR-TB/RR-TB currently include:Category 1—A bedaquiline-based injection-shorter treatment regimen (STR) (9 to 12 months) reserved for MDR-TB/RR-TB patients who have not been previously treated with second-line drugs and in whom resistance to fluoroquinolones and second-line injectable agents has been excluded. Drug options for shorter treatment regimen include an intensive phase of 4 months (extended to 6 months in case of delayed sputum smear conversion) containing high-dose gatifloxacin or moxifloxacin, kanamycin, prothionamide, clofazimine, high-dose isoniazid, pyrazinamide, and ethambutol followed by a continuation phase of 5 months containing gatifloxacin or moxifloxacin, clofazimine, ethambutol and pyrazinamide [12].Category 2—The longer treatment regimens (18 to 20 months) based on core backbone agents but individualized depending on age, fluoroquinolone resistance, and site of disease.

According to standard of care, patients with MDR-TB are managed as in-patients at central MDR treatment facilities (which include Mulago and Lira hospitals) in the intensive phase of treatment after which they are discharged and required to report to the central MDR treatment facility monthly for review and drug refills. Following discharge, during the continuation phase, patients are required to report daily to the nearest private or public facility registered under DOT programme [13]. Monthly reviews during routine care include safety laboratory investigations including a full blood count, liver and renal function tests, sputum culture, DST and adherence counseling.

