### Data collection plan

All participants will be reviewed by the study team monthly during routine visits (Table 3). On the initial visit, participants will be taken through a screening questionnaire to assess eligibility. Patients found to be eligible will then be taken through the informed consent process in the language of their preference. Enrolled participants will provide demographic information including age and gender. At each monthly study visit, participants will be taken through an interviewer-led questionnaire to capture clinical history (reported adverse events, treatment outcomes) and adherence information (adherence data downloads from MEMS devices, adherence data from TB treatment cards, pills counts, and participant-reported adherence on days of treatment missed). Adherence data will be used to provide tailored counselling for each participant to encourage treatment completion and this data will be shared with the participant’s primary clinician.

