### Statistical: outcomes

#### Adherence assessment

The primary outcome is the overall adherence rates among MDR-TB patients on self-administered therapy and on DOT. For the participants on the intervention arm, opening of the devices will be equated to a patient swallowing their medication and adherence will be derived from the number of days the device was opened as a proportion of the total number of days in the entire period of their MDR-TB treatment. Patients on the intervention arm will be required to take no less than 70% of their medication to be considered as having good adherence. For participants on the control arm (DOT), adherence information will be obtained from their TB treatment cards. Adherence rates will be calculated from the number of days that they report to the DOTS facility as a proportion of the total number of treatment complaint days in the entire period of their MDR-TB treatment. Participants who take their medication at least 80% of the time (missing no more than 5 days each month) will be considered as having good adherence.

The primary analysis will be a comparison of overall adherence in each arm. Adherence by self-administration (proportion of expected openings of the MEMS devices) and DOT (proportion of DOT visits) will also be compared at 2 months and 6 months in the intervention and control arms. The chi-square test and 1-way analysis of variance models will be used to compare outcomes by randomization arm. We shall use independent samples *t*-test to test for statistical difference mean adherence rates in the patient in the intervention and control arms. We will use an intent-to-treat approach (analysed all participants regardless of drug refills) to compare adherence outcomes by randomization arm using a generalized estimating equations model using repeated measures with identity link, exchangeable correlation structure and robust variance estimates.

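### The primary adherence ratio is defined differently in the two arms, and no rule says how in-patient days count, so the between-arm difference can move by as much as the 10-point margin or more

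*Protocol article*

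**What the plan says.** The Adherence assessment section gives two formulas for the primary outcome. For self-administration the ratio is "the number of days the device was opened as a proportion of the total number of days in the entire period of their MDR-TB treatment". For DOT it is "the number of days that they report to the DOTS facility as a proportion of the total number of treatment complaint days". The DOT sentence also runs over the whole course: "total number of treatment complaint days in the entire period of their MDR-TB treatment". In the abstract's methods the same term is what is measured for DOT, not what it is divided by: "treatment complaint days as recorded in the TB treatment card in the control arm". The Adherence assessment section also plans to compare expected device openings with DOT visits at 2 and 6 months.

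The section on diagnosis and management of MDR-TB says that, under standard of care, patients are "managed as in-patients at central MDR treatment facilities (which include Mulago and Lira hospitals) in the intensive phase of treatment", and that daily reporting to a DOT facility begins after discharge. For the shorter regimen it gives an intensive phase of 4 months, extendable to 6, and a continuation phase of 5 months.

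The trial-specific sections read differently. The Control arm section and Table 1 describe daily DOT at a nearby facility and mention no admission. In the control arm the card is ticked for each visit to the health centre. In the intervention arm both devices are handed out at enrolment.

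The Sample size section declares non-inferiority if the lower 95% confidence limit for MEMS minus DOT lies above −10%.

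**The concern.** A non-inferiority comparison needs the same quantity measured in both arms. Here both parts of the ratio may differ by arm for reasons unrelated to whether patients take their drugs.

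- **Denominator.** One arm is divided by all treatment days. The other is divided by a term that, if it means compliant days, nearly repeats its own numerator.
- **In-patient time.** A DOT numerator made of facility visits cannot accrue on a ward, whereas a device issued at enrolment can be opened there. If participants are admitted as the standard-of-care text describes, the whole-course ratio and the 2-month comparison both include time when the DOT measure does not exist.

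The trial is open-label and the margin is 10 points. If a counting convention can move the contrast by that much, the non-inferiority conclusion could turn on the convention and not on adherence.

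**Working it through.** The plan gives no figure of its own on this point, so there is none to reproduce. The check asks what each reading of the definitions does to the contrast.

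**Inputs**
- Intensive phase 4 months (up to 6) and continuation phase 5 months, shorter regimen: Diagnosis and management of MDR-TB. Totals: 4+5 = 9 months, or 6+5 = 11 months if extended.
- Longer regimen 18 months: Determination of TB treatment outcomes. Its intensive-phase length is not given. Using 4 or 6 months is an assumption.
- Margin −10 points, MEMS minus DOT: Sample size. It is applied here to the difference in mean adherence.
- Let *w* be the in-patient share of treatment, and *a* the true outpatient adherence in an arm.

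**Reading A: the DOT denominator is compliant days.** Visits are divided by days recorded as compliant, and the card is ticked per visit, so the DOT ratio tends to 100% whatever the behaviour. Suppose true adherence is equal in both arms. At 90%, the contrast is 90 − 100 = −10 points. At 70%, it is 70 − 100 = −30 points. The bias is against self-administration.

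**Reading B: the DOT denominator is all treatment days, ward days are not DOT visits, and devices are used on the ward.** A DOT patient who misses nothing scores 1 − *w*, and a self-administering patient who misses nothing scores 100%. The bias favours non-inferiority.

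**Reading C: ward days count as taken in both arms.** Each arm's whole-course value is *w* + (1 − *w*)*a*, so the difference is (1 − *w*) times the outpatient difference. An overall −10 then corresponds to −10/(1 − *w*) in the outpatient phase.

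| In-patient / total months | 1 − *w* | B: highest possible DOT score | B: artefact (points) | C: outpatient difference at −10 overall |
|---|---|---|---|---|
| 4 / 9 | 5/9 | 55.6% | +44.4 | −10 × 9/5 = −18.0 |
| 6 / 11 | 5/11 | 45.5% | +54.5 | −10 × 11/5 = −22.0 |
| 4 / 18 (assumed) | 14/18 | 77.8% | +22.2 | −10 × 18/14 = −12.9 |
| 6 / 18 (assumed) | 12/18 | 66.7% | +33.3 | −10 × 18/12 = −15.0 |

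**2-month comparison.** Month 2 lies inside a 4-month intensive phase. If participants are admitted for that phase, there are no DOT-facility visits to count at that point.

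**The case against.** **The denominator is a slip.** The odd word is very probably a misprint for compliant, and nearby text suggests a sensible intent. The 2- and 6-month measures are described as proportions of expected openings and of DOT visits. The 80% rule is glossed by days missed per month, which implies a calendar-day base. The Control arm section has the team record doses taken and missed. This makes Reading A less likely to be what is run. It does not remove the problem, because the sentence defining the primary outcome still gives the arms different denominators and the slip has no single obvious correction.

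**The admission may not apply to participants.** The in-patient text describes routine care, and the regimen it details includes an injectable agent, while eligibility is limited to oral therapy. The abstract, the comparator section, the Control arm section and Table 1 all describe daily facility DOT without an admission. This stands, and Readings B and C depend on it. However, the in-patient text names Mulago and Lira, the trial's own sites, and nothing exempts participants. The sections conflict and must be reconciled.

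**Stronger inferences that the documents do not support.**
- *The −10 margin is diluted, or the design favours non-inferiority.* Dilution needs ward days to be credited as taken in both arms, which no section says. Reading A works the other way.
- *Pill count and self-report are the only measures common to both arms.* Study outcomes also lists drug concentrations for both arms.
- *The primary window should start at discharge.* That would condition on a post-randomisation event. The intensive phase is extended for delayed smear conversion, which adherence may affect, and deaths in hospital would drop out.

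**Conclusion.** The point holds. As written, the primary outcome is a different ratio in each arm, over a period in which the control measure may not exist for part of the time. This is a stated definition, not detail left to an analysis plan.

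The size and direction depend on the reading:
- About −10 to −30 points against self-administration if DOT tends to 100% and true adherence is 90% to 70% in both arms.
- A ceiling of 56% for a fully adherent DOT patient on the 4+5-month regimen, favouring non-inferiority, if ward days are treatment days without a visit.
- About −18 points allowed in the outpatient phase on that regimen if ward days count as taken in both arms, or about −13 for 4 of 18 months.

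The last two rest on the standard-of-care in-patient phase applying to participants. The 18-month figure also assumes the same intensive-phase length. The mismatch in denominators needs neither assumption. The documents do not establish a single direction of bias.

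**What to change.** 1. Define adherence identically in both arms: days with a dose recorded divided by days a dose was prescribed, for all randomised participants from enrolment.
2. Reconcile the in-patient text in Diagnosis and management of MDR-TB with the Intervention arm section, Table 1 and the Control arm section, and state where participants are during the intensive phase.
3. Apply one identical rule for in-patient days in both arms, for example ward doses taken from the ward record in both. Because that rule brings in the weighting of Reading C, justify the 10-point margin for the window chosen.
4. Pre-specify outpatient-phase adherence as a sensitivity analysis, not as the primary window.
5. Re-time or drop the 2-month DOT-visit comparison if patients are then on the ward.
6. Add a supportive between-arm comparison of pill count. The Data collection plan already lists "adherence data from TB treatment cards, pills counts, and participant-reported adherence on days of treatment missed" for the monthly visits.

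Cost: a protocol amendment through the ethics committee (enrolment is reported at 70%), a recorded discharge date, access to ward dosing records if that rule is chosen, and a little extra analysis.

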## Specific objectives

The primary objective of the study is to determine if adherence to MDR-TB treatment among patients on self-administered therapy (measured by MEMS technology) is non-inferior to that among patients on directly observed therapy (DOT). The secondary objectives of the study include determining the correlation between MDR-TB drug serum concentrations and adherence as measured by MEMS technology and comparing treatment outcomes between MDR-TB patients on self-administered therapy and standard DOT

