### Sample size

Based on records from the NTP, treatment success rate for MDR-TB is 77.9%; from clinical trials, adequate adherence has been defined as 76–80% adherence rate; and from a meta-analysis, it has shown that 70% of patients on MDR-TB therapy are adherent [14, 15]. Our sample size calculation assumed that the adherence rate for the patients using MEMS technology is ≥ 70%, with study power of 0.9, precision of 0.05, and 20% loss to follow-up rate. We therefore require a sample size of 164 patients (82 in each arm) to demonstrate a 19% increment in MDR-TB treatment success. The intervention (MEMS technology) approach is considered non-inferior (19%) to the control (DOT) approach if the lower limit of the 95%CI of the difference between the two groups (i.e. MEMS group minus DOT group) is > −10%.

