#### Secondary outcomes

To assess correlation of specific MDR-TB drug serum concentrations with observed adherence, bedaquiline and linezolid pre-dose concentrations (C_trough_) will be used. To cater for those who may be adherent but have low bedaquiline or linezolid concentrations, we will use of cut-off value of bedaquiline C_trough_ from previous studies, below which a participant will be classified as non-adherence. Linezolid will be used to assess more recent adherence than bedaquiline.

We will compare time to sputum culture conversion in the intervention and control arm using time to event analysis. We shall also use chi-square testing to compare treatment success rates in the intervention and control arms. Treatment success will be evaluated using a composite outcome that includes TB cure (for microbiologically diagnosed patients) and TB treatment completion (for clinically diagnosed TB). We will undertake per-protocol and intention to treat analyses to compare TB cure rates in the two study arms. We will determine the proportions of patients retained in care of retention in care at 2 and 6 months in the two study arms using chi-square tests. Study outcomes by randomization arm will be compared using a generalized estimating equations (GEE) model using repeated measures with identity link, exchangeable correlation structure and robust variance estimates. Adjusted coefficients along with their corresponding 95% CIs will be generated. Statistical significance will be set at the *P* < .05 level and statistical analyses performed using Stata version 14 (StataCorp, College Station, TX, USA).

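### The −10% non-inferiority rule is assigned to no single adherence analysis and no single scale, and a per-protocol analysis is planned only for cure

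*Protocol article*

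**What the plan says.** All references are to the Protocol article.

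- **Specific objectives.** The primary objective is to find out whether adherence on self-administered therapy "is non-inferior to that among patients on directly observed therapy (DOT".
- **Sample size.** Non-inferiority is concluded if the "lower limit of the 95%CI of the difference between the two groups (i.e. MEMS group minus DOT group) is > −10" per cent. Neither the outcome being differenced nor the model that supplies the interval is named. The sentence before it sizes the trial "to demonstrate a 19% increment in MDR-TB treatment success", which is a different outcome.
- **Adherence assessment.** Adherence is defined as a proportion of treatment days. It is also dichotomised into good adherence, with a 70% figure for the intervention arm and an 80% figure after the control-arm text. The primary analysis is described only as a comparison of overall adherence. For the tests, "The chi-square test and 1-way analysis of variance models will be used to compare outcomes by randomization arm". A t-test for a difference in mean adherence follows, and then an intention-to-treat analysis "to compare adherence outcomes by randomization arm using a generalized estimating equations model using repeated measures with identity link". Non-inferiority, the margin and the interval rule do not appear in this section.
- **Secondary outcomes.** "We will undertake per-protocol and intention to treat analyses to compare TB cure rates in the two study arms". The same section says that 95% intervals for adjusted GEE coefficients will be produced and sets significance at P < .05.

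**The concern.** A non-inferiority conclusion needs one estimate, on one scale, with an interval that is compared with the margin. Here the rule is in one section and the analyses are in another, with nothing joining them. This goes beyond detail left to an analysis plan, because the article itself lists difference tests for a non-inferiority objective and gives a margin without an endpoint.

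Two things are at stake. First, the p-values of a chi-square test, an ANOVA or a t-test address the hypothesis of no difference, which is not the primary question. Secondly, ten points of mean percentage of days and ten points in the share of good adherers are different hypotheses. With both scales open and the analyses unranked, the choice could be made after the data are seen, in a trial where the Blinding section says that even the data manager is unblinded.

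A smaller matter is the analysis set. In a non-inferiority comparison, a per-protocol result is the usual companion to intention to treat. The article plans one for cure, a secondary outcome, but states none for adherence.

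**Working it through.** **Inputs from the protocol:** 82 per arm; 20% loss, so 82 × 0.8 = 65.6, taken as 66 per arm; margin 10 points; two-sided 95% interval; assumed adherence of at least 70% with MEMS; treatment success 77.9%; the 80% good-adherence figure.

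**Assumptions:** equal true rates in both arms for the power figures, because no DOT adherence rate is given; SD of 10 to 30 points for percentage of days, because no SD is given; normal approximation throughout.

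**1. Does the plan's own figure settle the scale?** No. Take 70% versus 89% (the 19-point increment), 90% power, and the stated 0.05 read as two-sided alpha:

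n = [1.96·√(2·0.795·0.205) + 1.2816·√(0.70·0.30 + 0.89·0.11)]² / 0.19² = 92.8, so 93 per arm. After 20% loss this is 93/0.8, or 117 per arm and 234 in total, not 164.

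Starting from 77.9% versus 96.9% gives 158. None of the readings tried that keep every stated input returns 164. That is a separate matter. It is relevant here only because the sample size cannot show which scale the margin was meant for.

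**2. What a non-significant difference test says about the margin.**

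P(non-significant) ≈ 1 − Φ(δ/SE − 1.96), with SE = √[(p₁q₁ + p₂q₂)/n].

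- True 70% v 60%, n = 82: SE = √(0.45/82) = 0.0741; δ/SE = 1.350; 1 − Φ(−0.610) = 0.73.
- Same rates, n = 66: SE = 0.0826; δ/SE = 1.211; 1 − Φ(−0.749) = 0.77.
- True 70% v 55%, beyond the margin, n = 82: SE = √(0.4575/82) = 0.0747; δ/SE = 2.008; 1 − Φ(0.048) = 0.48.
- Same rates, n = 66: SE = 0.0833; δ/SE = 1.802; 1 − Φ(−0.158) = 0.56.

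At exactly the margin, the interval rule would declare non-inferiority in about 2.5% of trials by construction.

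**3. Power for the −10 rule on the proportion scale.**

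Power = Φ(0.10/√(2pq/n) − 1.96).

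| Rate in both arms | n = 66 | n = 82 |
|---|---|---|
| 70% | Φ(1.254 − 1.96) = 24% | Φ(1.397 − 1.96) = 29% |
| 77.9% | Φ(1.384 − 1.96) = 28% | Φ(1.545 − 1.96) = 34% |
| 80% | Φ(1.436 − 1.96) = 30% | Φ(1.601 − 1.96) = 36% |

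**4. Power for the −10 rule on the mean scale.**

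Power = Φ(10/(SD·√(2/n)) − 1.96).

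| Assumed SD | n = 66 | n = 82 |
|---|---|---|
| 10 | Φ(5.745 − 1.96), over 99% | Φ(6.403 − 1.96), over 99% |
| 20 | Φ(2.872 − 1.96) = 82% | Φ(3.202 − 1.96) = 89% |
| 30 | Φ(1.915 − 1.96) = 48% | Φ(2.134 − 1.96) = 57% |

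**5. How many distinct analyses there are.** With two arms, one-way ANOVA and the equal-variance t-test are the same test. The list therefore reduces to three kinds: a categorical test, a comparison of means and a repeated-measures model. Only the last is described in a form whose arm coefficient is directly a difference.

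**The case against.** The strongest reply is that everything needed is already in the article. The rule is an interval rule, adherence is named as the primary outcome, and an identity-link GEE by arm yields a difference whose 95% interval can be held against −10%. On this view one linking sentence is missing, and the analysis plan may supply it. Much of this stands. A reader might infer that the plan has no means of testing non-inferiority, and that would be wrong. What remains is that the article never gives the GEE this role, does not say which adherence measure it models, and lists the difference tests beside it as equals.

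Other stronger readings also lack support:

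- **P < .05 as the primary decision rule.** The threshold appears under Secondary outcomes, and the stated criterion for non-inferiority is the interval. Nowhere does the article say that a non-significant test will count as non-inferiority. The 73% figure shows why those p-values cannot answer the question, not what the investigators intend.
- **Chi-square as the test of good adherence.** This is inferred from the type of test, since the text says only that outcomes are compared.
- **Intention to treat diluted by crossover.** No section describes crossover between the two modes or gives a rate for it.
- **No covariate adjustment.** Secondary outcomes mentions adjusted coefficients, and the missing-data section implies covariates in the primary model. Which covariates are used is ordinary analysis-plan content.

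On the figures, 66 per arm may be too low, because withdrawn participants are to be replaced and partial data are kept. The results for 82 per arm are therefore shown as well, and they lead to the same conclusion.

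**Conclusion.** The concern holds in this form: the article sets a non-inferiority objective and a −10% interval rule, gives adherence several unranked analyses, and does not say which analysis or which scale carries the rule.

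The consequence is material. Power for the same 10 points is 24–30% on the proportion scale with 66 per arm (29–36% with 82), and 48% to over 99% on the mean scale with 66 per arm (57% to over 99% with 82). The proportion figures assume equal true rates of 70–80%; power would be higher if self-administration were truly better. The mean-scale figures rest on an assumed SD of 10 to 30 points. The 73% in step 2 assumes 70% versus 60%.

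The per-protocol point is secondary. The article states intention to treat alone for adherence but does not rule out a supporting set.

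**What to change.** 1. Name one adherence scale for the primary outcome: mean percentage of days, or share with good adherence. If the share is chosen, the 70% and 80% figures must first be reconciled into a single definition for both arms.
2. Make the identity-link GEE arm difference (MEMS minus DOT) over the full treatment period, on that scale, the single primary analysis.
3. Declare non-inferiority only if the lower 95% limit of that difference is above −10 points on the named scale.
4. Label chi-square, ANOVA and the t-test as descriptive for this outcome.
5. As a supporting analysis, repeat the same interval in a per-protocol set defined by remaining on the allocated mode of administration. The set should not be defined by adherence, which is the outcome itself.

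The cost is changed wording and one extra analysis run, with no new data. The change should be dated before any comparison of adherence by arm is seen.
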